### Patient selection

#### Inclusion criteria

Age 18 years or olderAble and willing to provide informed consentPathologically proven diagnosis of prostatic adenocarcinomaUnfavourable intermediate- (with > 15% chance of node involvement based on the Memorial Sloan Kettering Cancer Centre nomogram [12]), high- or very high-risk prostate cancer based on the National Comprehensive Cancer Network classification (PSA > 20 ng/mL; or clinical cT3a or cT3b; or Gleason score 8–10)Eastern Cooperative Oncology Group performance status 0–1No prior history of pelvic irradiation, brachytherapy, cryosurgery, high-intensity focused ultrasound, transurethral resection of the prostate or radical prostatectomy

#### Exclusion criteria

Presence of nodal or distant metastasis, as confirmed by magnetic resonance (MR) or computed tomographic (CT) imaging of the abdomen/pelvis and bone scan within 90 days of randomizationPlan for adjuvant docetaxel post-radiotherapySerious medical comorbidities or other contraindications to HDR-BTPresence of inflammatory bowel diseasePresence of connective tissue diseaseMedically unfit for general anesthesiaUnable or unwilling to complete quality of life questionnaires

### Pre-treatment evaluation

History and physical examination by a radiation oncologist within 6 weeks prior to randomizationStaging investigations 90 days prior to randomization:
MR or CT abdomen/pelvisBone scanCompletion of quality of life forms (EPIC, IPSS, PORPUS-U and EQ-5D-5L) on the date of enrollmentAssessment of baseline toxicity using CTCAE version 5.0 prior to HDR-BTPatients undergoing treatment with ADT should have their HDR-BT scheduled for at least 2 months post-initiation of this therapy and no later than 6 months (up to 6 months of ADT prior to brachytherapy is acceptable for high-risk patients receiving long-term ADT). Patients with unfavourable intermediate-risk prostate cancer should receive HDR-BT between 2 and 4 months from ADT initiation.

### Data collection

All study data will be entered into Research Electronic Data Capture (REDCap), an electronic case report form database [13]. De-identified source documents will be uploaded directly into REDCap to support data entry.

### Treatment plan

Patients enrolled in this clinical trial will be treated with HDR-BT together with WPRT ± ADT. ADT will be at the discretion of the enrolling physician and its use should be initiated a minimum of 2 months prior to HDR-BT and no more than 4 months before HDR-BT for unfavourable intermediate-risk prostate cancer patients and no more than 6 months from the date of HDR-BT for high-risk patients receiving long-term ADT. The start date of ADT will correspond with the date of the first injection of a luteinizing hormone-releasing hormone (LHRH) agonist.

HDR-BT will be performed as previously described [14] to a dose of 15 Gy in a single fraction prescribed to the prostate. This dose and fractionation is widely used as a standard of care in the province of Ontario.

WPRT dose prescription (45 Gy in 25 fractions vs. 25 Gy in 5 fractions) will be selected according to which treatment arm the patient is randomized.

#### Androgen deprivation therapy

LHRH agonist use and total duration will be at the discretion of the enrolling physician with an acceptable range varying from 0 to 6 months for unfavourable intermediate-risk and 12–24 months for very high- or high-risk patients. Non-steroidal androgen receptor inhibitors (e.g. bicalutamide) is recommended to be used for up to 30 days prior to LHRH initiation.

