### Study design

This is a phase II, open label trial, randomizing 58 unfavourable intermediate-, high- or very high-risk prostate cancer patients between HDR-BT + conventionally fractionated (45 Gy in 25 fractions) WPRT (Arm 1: 29 patients) vs. HDR-BT + hypofractionated (25 Gy in 5 fractions) WPRT (Arm 2: 29 patients) (Fig. 1).

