**Fig. 1 Fig1:**
[figure not shown]
Study schema. Abbreviations: NCCN – National Comprehensive Cancer Network; MSKCC – Memorial Sloan Kettering Cancer Center

The study will employ a 1:1 randomization between Arm 1 and Arm 2 in a permuted block design without stratification with the size of the blocks known only to the statistician.

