### Consent process

A written informed consent will be obtained from all patients prior to radiotherapy (Additional file 1). Consents are allowed to be obtained after ADT initiation.

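### For high- and very high-risk men, an ADT duration chosen by the physician, with no stated commitment before open allocation, decides whether they are on ADT at the 1-year EPIC sexual comparison

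*Protocol article*

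**What the plan says.** The section Treatment plan covers every enrolled man: "Patients enrolled in this clinical trial will be treated with HDR-BT together with WPRT ± ADT". It leaves the decision to the enrolling physician and sets a lead-in: "ADT will be at the discretion of the enrolling physician and its use should be initiated a minimum of 2 months prior to HDR-BT". The upper limit on the lead-in is 4 months for unfavourable intermediate risk. For the higher-risk group it is "no more than 6 months from the date of HDR-BT for high-risk patients receiving long-term ADT".

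The section Androgen deprivation therapy repeats the discretion for both use and length ("LHRH agonist use and total duration will be at the discretion of the enrolling physician") and gives the acceptable range as "0 to 6 months for unfavourable intermediate-risk and 12–24 months for very high- or high-risk patients".

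Under Study design: "This is a phase II, open label trial". Allocation is 1:1 "in a permuted block design without stratification". Under Consent process: "Consents are allowed to be obtained after ADT initiation".

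The EPIC sexual domain at 1 year is a secondary endpoint (Secondary endpoints). The Analysis plan compares it between arms by a two-sample t-test for non-inferiority, or by a Wilcoxon test if the data are not normal.

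**The concern.** Whether a man is on ADT when he fills in the sexual domain may well affect his score, and fractionation has nothing to do with that. Randomization balances this only in what is settled before allocation. Total duration need not be. The physician knows the arm, and nothing in the article fixes the length of the course before the arm is revealed. If physicians tend towards longer courses in one arm, for example because they are less sure of cancer control with the newer schedule, the 1-year sexual comparison mixes ADT exposure with fractionation. Longer ADT in Arm 2 would count against non-inferiority; longer ADT in Arm 1 would favour it. The t-test named in the Analysis plan has no covariate to separate the two.

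For the PSA and biochemical endpoints the concern is narrower: longer ADT in one arm may delay failure there.

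**Working it through.** The plan gives no figure for ADT exposure at 1 year, so there is none to reproduce. Its 23 per arm, used below, is not in dispute: with margin 5, SD 5 and two-sided alpha 0.05, the exact t-test power is 0.8997 at 22 and 0.912 at 23 per arm, and 23/0.8 = 28.75 gives 29.

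**Step 1. When does the 1-year visit fall, counted from ADT start?**

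Inputs:
- ADT start to HDR-BT: 2–6 months for high risk, 2–4 for unfavourable intermediate risk (Treatment plan; Pre-treatment evaluation).
- HDR-BT to WPRT: 14–21 days (Treatment delivery).
- First to last day of WPRT: 32 days for 25 weekday fractions starting on a Monday, and 8 days for five fractions every other day. These counts are derived from the schedules and assume no breaks.
- Follow-up counts from the last day of WPRT (Follow-up evaluation), so 12 months are added.

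| Group | Earliest (Arm 2) | Latest (Arm 1) |
|---|---|---|
| High, very high risk | 2 + (14+8)/30.44 + 12 = 14.7 months | 6 + (21+32)/30.44 + 12 = 19.7 months |
| Unfavourable intermediate risk | 14.7 months | 4 + (21+32)/30.44 + 12 = 17.7 months |

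If weekends stretch Arm 2 to 10 days, the earliest figure becomes 14.8.

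**Step 2. Who is on ADT at that visit?**

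- High risk, 12-month course: ended 14.7 − 12 = 2.7 to 19.7 − 12 = 7.7 months earlier.
- High risk, 24-month course: still has 24 − 19.7 = 4.3 to 24 − 14.7 = 9.3 months to run.
- Unfavourable intermediate risk, at most 6 months: ended at least 14.7 − 6 = 8.7 months earlier.

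Only in the high- and very high-risk group does the permitted choice of duration decide ADT status at 1 year.

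**Step 3. And at 4 years, when PSA response is assessed?** A 24-month course ends 4.3–9.3 months after the 1-year visit. That is 36 − 9.3 = 26.7 to 36 − 4.3 = 31.7 months before the 4-year assessment. No course within the stated range is still running then.

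**Step 4. How large could the shift be?** The documents give neither an effect of ADT on the sexual score nor an arm imbalance, so both are assumed.

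Shift = effect × difference between arms in the proportion on ADT.
- Low: 10 × 0.10 = 1 point.
- Middle: 20 × 0.20 = 4 points.
- High: 30 × 0.30 = 9 points.

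The imbalance is across the whole arm, but only high- and very high-risk men can produce it. If they make up a share h of each arm, a 0.20 imbalance needs 0.20/h among them: 0.40 at h = 0.5 and 0.22 at h = 0.9 (h is assumed; the document gives no mix).

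**Step 5. What would a 4-point shift do?** As an illustration, take the 5-point margin, which the plan states only for bowel function, and 23 per arm. With SE = SD × √(2/23), the chance of declaring non-inferiority is Φ((5 − b)/SE − 1.96) when the arms are truly equal and the shift b counts against Arm 2. It is Φ(b/SE − 1.96) when Arm 2 is truly 5 points worse and the shift favours it.

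| SD | Equal arms, b = 0 → 4 | 5 points worse, b = 0 → 4 |
|---|---|---|
| 5 (the bowel value) | 0.92 → 0.10 | 0.025 → 0.77 |
| 15 (assumed) | 0.20 → 0.04 | 0.025 → 0.15 |

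Chance imbalance is a separate matter. Under a simple binomial with 23–29 per arm and 30–70% on ADT, a difference of at least 20 percentage points arises with probability about 0.11–0.18. The t-test's error rate already allows for that, so it is a reason to adjust for precision and no evidence of bias.

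**The case against.** Several points on the other side stand.

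- **Use is often settled early.** ADT, if given, starts at least 2 months before HDR-BT, and consent may follow its start. For a man already on ADT at consent, arm knowledge cannot affect the decision to begin. That order is allowed but not required, and it does not protect total duration, which can be set or changed later.
- **The sections can be read together.** The plus-or-minus sign in Treatment plan may be the general rule and the later ranges its limits, with the zero for unfavourable intermediate risk accounting for men without ADT. A reader might infer a flat contradiction on whether high-risk men may go without ADT. The text supports only an ambiguity: use is called discretionary, the 6-month limit is worded for high-risk men receiving long-term ADT, and their range has no zero.
- **Disease control.** A reader might infer that castration status differs by arm when disease control is assessed. The plan has no 1-year disease-control endpoint. PSA response is at 4 years, the rest are times to event, and Step 3 shows that permitted courses are over well before 4 years.
- **The full protocol and analysis plan are not shown.** Either may already record planned ADT or name covariates for the mixed models. The point therefore rests on what the article does state: discretion over duration, open allocation without stratification, and the two-sample test.
- **Differential prescribing is conjecture.** Nothing in the documents shows that it will happen, or in which direction.

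**Conclusion.** The point holds for one named secondary endpoint and one group of men. For high- and very high-risk patients, a duration left to the physician, with no stated commitment before open allocation, decides ADT status at the 1-year sexual comparison. The timing follows from the protocol's own intervals plus uninterrupted WPRT. The size does not: 1–9 points is a product of two assumptions, and recovery after stopping ADT, on which the document is silent, would change it. For the PSA and biochemical endpoints, the point goes no further than possible delay of failure under longer ADT.

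A reader might infer that the trial's main conclusion is at risk. The documents do not support that: the primary endpoint and the sample size concern EPIC bowel function, and nothing shown links ADT to it. This is a cheap improvement, not an obstacle to the trial.

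**What to change.** 1. Before allocation is released, record intended ADT use, the actual or planned date of the first LHRH injection, and planned total duration.
2. Adjust the 1-year EPIC sexual comparison for planned duration, in categories that separate courses planned to end before the 1-year visit from those planned to run past it. A single 12–24 month category would merge the very men who differ. Use the same cut in both arms: from ADT start, Arm 1's visit falls 32 − 8 = 24 days later than Arm 2's for identical lead-ins.
3. Repeat this adjustment as a sensitivity analysis for the PSA and biochemical endpoints.
4. Report actual duration, and reasons for departing from the plan, by arm. The covariate does not correct changes made after allocation; this report is what would reveal them. A recorded plan also helps to tell an extended course from the start of salvage ADT, an event in ADT-free survival.
5. Reconcile Treatment plan with the range in Androgen deprivation therapy for high- and very high-risk men. No ADT rule is proposed here.

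Cost: one extra entry at randomization, a slightly earlier statement of the ADT plan, documentation of departures, and one covariate in a small trial. No sample-size figure changes.

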#### HDR-BT planning and treatment

HDR-BT boost is a standard of care component of treatment in patients with unfavourable intermediate- and high-risk prostate cancer. This therapy will be delivered to all patients accrued in this study prior to WPRT. HDR-BT dose will consist of 15 Gy in a single fraction to the whole prostate. Patients with seminal vesicle involvement may have this organ included in the treated volume during brachytherapy at the discretion of the brachytherapist. The procedure should be performed under transrectal ultrasound-guidance. A total of three fiducial markers should be inserted in the left base, right mid-gland and left apex during the procedure. These markers will be used for prostate matching using cone beam CT and/or orthogonal kV images at the treatment unit when WPRT is being delivered.

The following dosimetric objectives should be pursued during HDR-BT:
Prostate V_100_ ≥ 95%; V_150_ < 40%; V_200_ < 15%Urethra D_10_ < 118%; Urethra D_max_ < 130%Rectum V_80_ < 1 cc

The number of catheters inserted should vary from 10 to 18 depending on prostate volume and shape.

#### Radiotherapy planning and treatment

##### Contouring

The prostate and at least the proximal 1 cm of the seminal vesicles should be included in the WPRT clinical target volume (CTV). The whole seminal vesicles are encouraged to be included in patients with high- or very high-risk prostate cancer. Seminal vesicles should be completely covered by the CTV in patients with stage cT3b disease.

RTOG guidelines will be used for elective nodal irradiation. Obturator, pre-sacral, external and internal iliac drainages should be included in the CTV. Inclusion of the common iliac drainage is allowed and at the discretion of the treating physician.

Elective drainages, prostate and seminal vesicles should be combined to form CTV45Gy for patients randomized to Arm 1 and CTV25Gy for patients in Arm 2.

The planning target volume (PTV) is the CTV plus a 6 mm isotropic margin.

Normal critical structures that must be contoured include: bladder, rectum (from its origin at the rectosigmoid flexure until the level of the ischial tuberosities), penile bulb, bilateral femora and bowel (including sigmoid).

##### WPRT planning

Plans will be developed for IMRT or VMAT delivery techniques using an inverse planning system. If available, VMAT plans are recommended due to more conformal dose distribution and faster treatment delivery. A conformal and uniform dose distribution covering prostate, seminal vesicles and lymph nodes should be prioritized (maximum point dose inside PTV < 108%).

##### Dosimetric aims

CTV 45Gy / 25Gy: V_100_ ≥ 99%PTV 45Gy / 25Gy: Ideal V_100_ ≥ 95%; Mandatory V_95_ ≥ 95%Conformity index (95% isodose line [42.75 Gy or 23.75 Gy] to PTV): Ideal < 1.3; Mandatory < 1.5

##### Critical organs at risk

Critical organs at risk and respective dose constraints are listed in Table 1. If the rectum and bladder constraints are not met, the PTV margin for prostate and seminal vesicles may be reduced to 5 mm.

**Table 1 Tab1:** Critical organs at risk and respective dose constraints

	Arm 1: 45 Gy in 25 fractions	Arm 2: 25 Gy in 5 fractions
Rectum	V_29_ < 50%	V_18_ < 50%
	V_35_ ≤ 30%	V_20_ ≤ 30%
	D_1 cc_ ≤ 46 Gy	D_1 cc_ ≤ 26 Gy
Bladder	V_29_ < 50%	V_18_ < 50%
	V_35_ ≤ 30%	V_20_ ≤ 30%
	D_1 cc_ ≤ 47 Gy	D_1 cc_ ≤ 26 Gy
Femurs	D_10 cc_ < 45 Gy	D_10 cc_ < 25 Gy
Bowel (including sigmoid)	V_45_ < 40 cc (acceptable 60 cc) D_1 cc_ ≤ 47 Gy	V_25_ < 40 cc (acceptable 60 cc) D_1 cc_ ≤ 26 Gy
Penile bulb	Mean dose < 35 Gy	Mean dose < 20 Gy

##### Treatment delivery

Patients randomized to Arm 1 will be treated with daily fractions of WPRT from Monday to Friday. Patients randomized to Arm 2 will be treated with WPRT fractions every other day. In both arms, WPRT should begin 2–3 weeks after HDR-BT.

Daily image guidance will be performed during treatment delivery. Prostate fiducials should be initially matched. Then, the surrounding soft tissue should be evaluated including the prostate-rectum interface. Lastly, position of the pelvic nodes should be assessed.

Treatments should be delivered preferably in units with a 6-degree couch capability. Bowel preparation should be available in case large amounts of stools or gas are present inside the rectum.

##### Quality assurance

In order to ensure patient safety and effective treatment delivery, a robust quality assurance protocol is incorporated. The following requirements must be completed for each patient:
Prior to treatment delivery, contours and plan will be peer-reviewed, either by another individual radiation oncologist or presented at genitourinary quality assurance rounds.All dose delivery for intensity-modulated plans (including arc-based treatments) will be reviewed before treatment by physics staff.Cone-beam CT and/or orthogonal kV images will be used on a daily basis to verify treatment positioning and pelvic organ filling.

### Consent process

A written informed consent will be obtained from all patients prior to radiotherapy (Additional file 1). Consents are allowed to be obtained after ADT initiation.

### Subject discontinuation and withdrawal

Subjects may voluntarily discontinue participation in the study at any time. If a subject is removed from the study, the clinical and laboratory evaluations that would have been performed at the end of the study should be obtained. If a subject is removed because of an adverse event, they should remain under medical observation as long as deemed appropriate by the treating physician.

### Follow-up evaluation and assessment of efficacy

The follow-up schedule is shown in Table 2. Day 1 of follow-up will correspond with the last day of WPRT. Additional imaging or laboratory investigations should be carried out at the discretion of the oncologist, based on findings in the history or physical examination. Additional treatment (e.g. salvage treatment with surgery or further radiotherapy) is at the discretion of the treating physicians, and will be captured in the case report form.

**Table 2 Tab2:** Study follow-up schedule

	Baseline^a^	First day of WPRT	Last day of WPRT	6 weeks post-WPRT	Follow up (months)^b^						
					6	12	18	24	36	48	60
Physical Examination	X			X	X	X	X	X	X	X	X
Imaging	X										
PSA	X				X	X	X	X	X	X	X
EPIC	X	X	X	X	X	X	X	X	X	X	X
IPSS	X	X	X	X	X	X	X	X	X	X	X
CTCAE	X	X	X	X	X	X	X	X	X	X	X
Survival and disease status					X	X	X	X	X	X	X
EQ-5D and PORPUS-U	x			x		x		x			

*Abbreviations*: *WPRT* whole pelvis radiotherapy, *PSA* prostate specific antigen, *EPIC* Expanded Prostate Cancer Index Composite, *IPSS* International Prostate Symptom Score, *CTCAE* Common Terminology Criteria for Adverse Events, *EQ-5D-5L* EuroQOL 5-Dimension 5-Level, *PORPUS-U* Patient-Oriented Prostate Utility Scale

^a^Baseline assessments to be completed prior to high-dose-rate brachytherapy

^b^Follow-up schedule determined based on day of last WPRT treatment

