In parallel to studies evaluating the role of WPRT in prostate cancer, radiotherapy technique has improved in the last few decades. Technological advances, such as intensity-modulated radiotherapy (IMRT), volumetric-modulated arc therapy (VMAT) and image-guided radiotherapy, have allowed radiation oncologists to more accurately target volumes while sparing more normal tissue. In conjunction with the favourable tumour radiobiology (i.e. a low alpha/beta ratio) of prostate cancer cells, researchers have investigated the role of hypofractionated treatments (> 2 Gy per fraction) in patients with prostate cancer. A recent randomized control trial involving multiple centres showed no difference in late toxicity and cancer control between ultra-hypofractionated (≥ 5 Gy per fraction) and conventionally fractionated radiotherapy to the prostate alone [9].

The use of ultra-hypofractionation in WPRT is still in its infancy and the toxicity associated with this strategy is unclear. To our knowledge, only two small, single-arm studies have reported outcomes associated with this treatment. In both of them, a simultaneous boost was delivered to the prostate and proximal seminal vesicles. In the SATURN study [10], authors reported an acceptable toxicity profile with this approach, while authors from the FASTR trial had higher than anticipated late toxicities resulting in early trial discontinuation [11].

Currently, clinical trials such as the French SHORT trial (NCT03417336) randomize higher-risk prostate cancer patients between HDR-BT + WPRT (25 Gy in 5 fractions) versus stereotactic radiotherapy to the prostate + WPRT. However, there is no current data comparing the toxicity profile between conventionally fractionated WPRT (45 Gy in 25 fractions) versus hypofractionated WPRT (25 Gy in 5 fractions), and long-term bowel toxicity associated with this approach is unknown. Moreover, the genitourinary safety profile associated with hypofractionated WPRT plus HDR-BT boost has not yet been fully investigated.

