### Endpoints

#### Primary endpoint

Late bowel toxicity and quality of life measured using the Expanded Prostate Cancer Index Composite (EPIC) bowel function subdomain at 1 year post-treatment

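### No utility is measured during pelvic radiotherapy or between 6 weeks and 12 months, so short-lived differences between arms cannot enter the cost-effectiveness analysis

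*Protocol article*

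**What the plan says.** The Secondary endpoints section of the protocol article includes a cost-effectiveness comparison of the two arms. The same list sets PORPUS-U and EQ-5D-5L at 6 weeks, 1 year and 2 years after treatment. Table 2 (Follow-up evaluation and assessment of efficacy) agrees: the row "EQ-5D and PORPUS-U" is marked at baseline, 6 weeks, month 12 and month 24.

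EPIC, IPSS and CTCAE are marked at those four visits and at seven more: the first and last day of WPRT and months 6, 18, 36, 48 and 60.

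Four timing rules bear on the point:
- The footnote to Table 2 has "Baseline assessments to be completed prior to high-dose-rate brachytherapy".
- The Treatment delivery section says "WPRT should begin 2–3 weeks after HDR-BT" in both arms.
- The same section separates the arms: "Patients randomized to Arm 1 will be treated with daily fractions of WPRT from Monday to Friday" and "Patients randomized to Arm 2 will be treated with WPRT fractions every other day".
- Follow-up is counted from the end of treatment: "Day 1 of follow-up will correspond with the last day of WPRT".

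**The concern.** A within-trial QALY is an area under a utility curve drawn through the measured points. Here the curve runs straight from a value before HDR-BT to one taken 6 weeks after the last WPRT fraction, and then straight to month 12. A loss of utility that has gone by the next measurement contributes nothing.

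The treatment phase is where the arms differ by design, with 25 weekday fractions against 5 on alternate days. The Background section gives convenience as a main attraction of the short schedule. The cost side will register the saved fractions, while the utility side cannot register how the men felt during treatment. The second gap, about ten and a half months, would hide any problem that appears after 6 weeks and settles before the 1-year visit.

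This differs from a detail left to an analysis plan. A plan can choose a horizon or an interpolation rule, but it cannot recover questionnaires that were never given.

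**Working it through.** The article gives no figure for this endpoint, so there is none to reproduce. The check compares rows of Table 2, does calendar arithmetic on the schedules, and illustrates the size with assumed utility dips.

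**1. Visits.** EPIC has 11 and the utility instruments have 4. The 11 − 4 = 7 visits without utilities are the first and last day of WPRT and months 6, 18, 36, 48 and 60.

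**2. Length of WPRT.**
- Arm 1: 25 weekday fractions from a Monday, without gaps, span 4 × 7 + 5 = 33 days.
- Arm 2: 5 fractions on alternate days span 1 + 4 × 2 = 9 days if weekends are used, and 10 to 12 days if only weekdays are used, depending on the starting day.
- Difference: 33 − 12 = 21 to 33 − 9 = 24 days.

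**3. Interval from baseline to the 6-week utility.** Take baseline on the day of HDR-BT, a gap of 14 to 21 days to WPRT, and 42 days after it.
- Arm 1: 14 + 33 + 42 = 89 to 21 + 33 + 42 = 96 days.
- Arm 2: 14 + 9 + 42 = 65 to 21 + 12 + 42 = 75 days.

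These are minimum values. The Pre-treatment evaluation section has the questionnaires completed at enrolment, which may be earlier.

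**4. Treatment-phase QALY not seen, between arms.** All dips are assumptions and are taken to have resolved by 6 weeks.

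| Assumption | Formula | QALY |
|---|---|---|
| Dip of equal depth in both arms (0.05 to 0.10), triangular over the interval in step 3 | dip × (21 to 24 days) / 365.25 / 2 | 0.0014 to 0.0033 |
| Constant difference of 0.05 to 0.20 over the 24 extra treatment days | difference × 24 / 365.25 | 0.0033 to 0.0131 |
| Constant difference of 0.05 to 0.20 over all 33 days of Arm 1 | difference × 33 / 365.25 | 0.0045 to 0.0181 |

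The overall range is about 0.001 to 0.02 QALY.

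**5. Direction.** With dips of equal depth, the unseen loss is larger in Arm 1 because its interval is longer, so the omission would work against the experimental arm. Under the triangle assumption the sign reverses if the dip in Arm 2 is deeper by more than the ratio of the intervals. That ratio runs from 96/75 = 1.28 to 89/65 = 1.37. The documents give no basis for saying which case applies.

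**6. Gap from 6 weeks to month 12.** Its length is 365.25 − 42 = 323.25 days. A triangular between-arm loss that starts at 6 weeks and has gone by month 12 has area peak × 323.25 / 365.25 / 2, wherever the peak falls. Assumed peaks of 0.05 and 0.10 give 0.022 and 0.044 QALY.

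**7. After month 24.** The visit schedule continues for 60 − 24 = 36 months without utilities. No QALY figure is attached, because it would need a horizon that the article does not state.

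**The case against.** The two sections agree, so the schedule is consistent and evidently deliberate, and more visits could be called a reviewer's preference. Utilities are taken at 6 weeks, the acute time point, and at 12 months, where the primary endpoint is set: "bowel function subdomain at 1 year post-treatment". Every EPIC, IPSS and CTCAE endpoint listed is set at 6 weeks, 1 year or 2 years, and utilities exist at all three. EPIC is collected in the gaps, so utilities might be mapped from it.

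Most of this stands. There is no contradiction, and the main comparison points are covered. Mapping is possible, but it replaces a measurement that could be taken at the same visit with a model. The two gaps remain.

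A reader might be tempted to infer three stronger points, and the documents support none of them:
- **Utilities are missing where the arms are most likely to differ.** The documents do not say when that is. They expect similar toxicity, with biologically equivalent doses at alpha/beta 3 of 45 × (1 + 1.8/3) = 72 Gy and 25 × (1 + 5/3) = 66.67 Gy.
- **Late harm is left out.** The Background section says "long-term bowel toxicity associated with this approach is unknown" but names no years, and the protocol measures late bowel toxicity at 1 year. A deficit present at month 24 would show in the month-24 utility and could be carried forward. Only one that emerges later would be missed, and only with a horizon beyond two years.
- **The omission favours the experimental arm.** That needs worse toxicity with the short schedule. The unmeasured treatment phase is longer in the control arm, so the omission could equally hide a benefit of the short schedule.

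**Conclusion.** The point holds as a minor weakness in the design of one secondary endpoint. Utilities are absent throughout WPRT and between 6 weeks and 12 months, so transient between-arm differences in those periods cannot enter the QALYs.

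The size is roughly 0.001 to 0.02 QALY for the treatment phase and 0.02 to 0.04 QALY for the later gap, with unknown direction. These figures rest on assumed dips of 0.05 to 0.20, full recovery by the next utility visit, straight-line interpolation, and QALYs built from EQ-5D-5L or PORPUS-U. The article does not state that last choice, although it names no other utility source. Whether the stop at 24 months matters depends on the horizon. The non-inferiority comparison and the 58-patient target are untouched.

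**What to change.** In Table 2, add EQ-5D-5L on the last day of WPRT and at month 6, completed together with the EPIC already due. The endpoint times in the Secondary endpoints list can stay as they are, since the added values serve only the QALY calculation. The first day of WPRT and month 18 can be left out. On the first day of WPRT both arms have had the same HDR-BT and the fractionation contrast is only beginning. Month 18 lies between two measured visits.

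State the cost-effectiveness horizon. If it goes beyond 24 months, also add EQ-5D-5L at the existing 36-, 48- and 60-month visits. If it does not, limit the cost-effectiveness conclusion to 24 months and say so.

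The cost is a minor amendment for one short questionnaire at two existing visits, or five with the longer horizon, with no new visits or staff. The drawbacks are slightly more questionnaire burden and missing values for men who have already passed the added visits. For those men, report how many lack the values and calculate their QALYs from the four original time points.
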